#### 2.1.5. Recruitment

Forty inpatients with PSCI at Zhujiang Hospital, Southern Medical University will be recruited. The participants will be screened by a dedicated individual for those who meet the inclusion and exclusion criteria and are willing to receive TMS treatment. The participants will receive information in both written and verbal formats about the purpose and procedures of the study once their verbal consent has been confirmed. In this study, no biological specimens will be collected for storage, and no severe adverse effects on the participants are expected (Lefaucheur et al., 2020). The study will begin with a baseline assessment followed by random allocation after written informed consent is obtained from the participants.

#### 2.1.6. Randomization and blinding

Using a random number sequence generated using SPSS 25.0 software, all eligible patients will be randomly assigned to one of two treatment groups. The allocation and detailed TMS protocol will be known only to the two doctors who will perform TMS stimulation but will be blinded to the patients and other members of the study staff (such as outcome assessors or data analysts). Doctors performing TMS interventions will not be involved in any other aspect of the study, such as patient recruitment, randomization, allocation, outcome assessment, or data analysis.

### 2.2. Interventions

Transcranial magnetic stimulation treatments will be delivered by a magnetic simulator (Magneuro100, VISHEE Medical Technology Co., LTD, Nanjing, China) with a figure-8 coil. Each patient will receive TMS stimulation in the afternoon for 10 consecutive days. The left DLPFC (F3) will be the target site to stimulate the left prefrontal cortex according to the international 10/20 EEG recording system (Kim et al., 2010). The intensity will be set at 80% of the resting motor threshold in both the rTMS and iTBS groups (Shajahan et al., 2002; Kim et al., 2010).

#### 2.2.1. rTMS protocol

The 5 Hz rTMS parameters include 2-s trains (10 pulses) at an intertrain interval of 8 s, repeated every 10 s for a total of 10 min and 600 pulses.

#### 2.2.2. iTBS protocol

The iTBS parameters include three continuous pulses at 50 Hz, repeated at 5 Hz (2 s on, 8 s off) for a total of 192 s and 600 pulses. After the stimulation is completed, the direction of the coil is turned 90°, and a sham stimulation lasting 408 s is conducted in order to ensure the consistency of treatment time such that all patients are blinded to the experimental protocol.

#### 2.2.3. RMT

The resting motor threshold (RMT) refers to the minimum stimulus intensity that can evoke a response at least 50% of the time in a given number of trials (usually 10 trials). The patients will be asked to relax with their eyes open. During the recording process, the coils will be systematically moved (mapped) over the primary motor cortex until the maximal consistent response of the contralateral first dorsal interosseous muscle is detected. The RMT between the first dorsal interosseous bone and the minimum intensity is defined as the ability to elicit motor-evoked potentials of at least 50 mV in 5 out of 10 consecutive treatments (Rossini et al., 2015).

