#### 2.3.2. Resting EEG measurements

A resting EEG is a graphical representation of the spontaneous electrical activity of a population of brain cells. It is obtained by magnifying and recording spontaneous biopotentials of the brain from the scalp using sophisticated electronic equipment (Höller and Nardone, 2021). EEG signals will be recorded using an EEG cap equipped with 64 Ag/AgCl electrodes, arranged according to the Extended International 10–20 electrode placement system (Tamburro et al., 2020). A 5-min EEG recording will be conducted with participants seated comfortably in a sound-insulated, dimly lit room with their eyes closed. All channels will be referenced online to the bilateral mastoid and amplified using an amplifier (Compumedics Neuroscan, Neuroscan 8050). Data will be sampled at 2,048 Hz, with impedances kept below 10 kΩ for all channels throughout data collection.

The acquired EEG signals will be analyzed offline using MATLAB2013b. Given previous evidence that oscillatory dynamics are affected by rTMS (Thut et al., 2011; Veniero et al., 2011; Chota et al., 2021) and are closely related to cognitive improvement (Klimesch et al., 1993; Richard Clark et al., 2004; Iliopoulos et al., 2020), we will analyze the power spectrum and functional connectivity of each oscillation within and between hemispheres, between groups, and pre- and post-treatment. Oscillation ratios, such as θ/α ratio, θ/γ ratio, and (α + β)/(θ + δ) ratio will be further analyzed (Coben et al., 1985; Moretti et al., 2013; Sato et al., 2022).

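### The resting motor threshold that sets the dose in both arms is printed with a 50 mV amplitude criterion, very probably a slip for 50 microvolts

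*Protocol article*

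**What the plan says.** Section 2.2 of the protocol article ties the dose to the RMT: "The intensity will be set at 80% of the resting motor threshold in both the rTMS and iTBS groups". Section 2.2.3 then describes the RMT twice.

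- Its opening sentence gives a general definition without any amplitude: "the minimum stimulus intensity that can evoke a response at least 50% of the time in a given number of trials", usually 10 trials.
- After saying that the coil is moved until "the maximal consistent response of the contralateral first dorsal interosseous muscle is detected", it gives an operational definition: "the ability to elicit motor-evoked potentials of at least 50 mV in 5 out of 10 consecutive treatments".

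The second definition contains the only amplitude criterion in the article. No other section gives a value, in millivolts or microvolts, against which to check it.

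**The concern.** An amplitude of 50 mV is implausibly large for a threshold response in a small hand muscle at rest. A threshold is meant to mark the lowest intensity that just produces a response. A cut-off above the largest response the muscle can give cannot mark such a point.

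The figure matters because it belongs to the dosing rule. Stimulation intensity in the rTMS and the iTBS group is a fixed percentage of the RMT, so the definition of the RMT defines the dose. Anyone who wants to repeat the intervention, or to check that it was given as planned, would take the criterion from this sentence.

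**Working it through.** **Inputs**

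- Printed amplitude criterion: at least 50 mV (section 2.2.3).
- Printed response rate: 5 of 10 stimulations (section 2.2.3).
- General response rate: at least 50% of usually 10 trials (section 2.2.3, opening sentence).
- Recording site: contralateral first dorsal interosseous, a hand muscle (section 2.2.3).
- Dose: 80% of RMT in both arms (section 2.2).
- Largest response obtainable from a hand muscle: about 1 to 30 mV. This is an assumption from general measurement knowledge; the documents give no figure.

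**Step 1: is the response rate consistent?** 5 / 10 = 50%, which agrees with the opening sentence. Only the amplitude is in question.

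**Step 2: can the printed amplitude be reached?** At the bottom of the assumed range, 50 / 1 = 50 times the largest response. At the top, 50 / 30 = 1.7 times. The criterion is out of reach over the whole range. A narrower assumption of 5 to 20 mV gives the same answer (50 / 5 = 10 times; 50 / 20 = 2.5 times). The conclusion would reverse only if the muscle could produce 50 mV or more.

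**Step 3: what repair is simplest?** Keep the number and change the prefix. 50 mV = 50,000 microvolts, and 50,000 / 50 = 1,000. The repaired criterion, 50 microvolts = 0.05 mV, is a twentieth of even the lowest assumed maximum (0.05 / 1 = 5%). That is the right order for a threshold response: attainable, and small against the maximum.

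**Step 4: does the document support a drafting slip?** The sentence has other errors. It calls the first dorsal interosseous a bone, although the sentence before calls it a muscle. It counts treatments where the opening sentence counts trials. It equates a threshold with an ability.

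**Step 5: could the text conversion have done it?** Section 2.3.2 keeps the ohm sign and Greek letters intact, for example "such as θ/α ratio, θ/γ ratio", so Greek symbols were not lost in general. On the other side, one letter of a cited name in the Introduction looks corrupted, and no micro sign appears anywhere to test. An artefact is unlikely but cannot be ruled out.

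**The case against.** The strongest reply is that the error cannot be shown from the documents alone. The two definitions in section 2.2.3 do not contradict each other. That 50 mV is unreachable, and that microvolts were meant, both come from outside, and the guideline cited there cannot be seen. This stands as a limit on certainty. It is why the range is given as an assumption, the intended unit is called very probable, and the fix begins by confirming it. It does not rescue the figure, because the result is the same over the whole assumed range and the sentence is visibly garbled in other places.

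The second reply is that nothing would go wrong in practice, and most of it stands. A reader might infer that no threshold could be found and no intensity set. The documents do not support that: the opening sentence of section 2.2.3 gives a workable definition without an amplitude, and an operator trained in the technique would probably apply the right unit.

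A reader might also infer from "The allocation and detailed TMS protocol will be known only to the two doctors who will perform TMS stimulation" in section 2.1.6 that these two doctors work from the faulty sentence. The article does not say so. It condenses a fuller protocol, in which the criterion may be correct.

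**Conclusion.** The amplitude criterion is wrong as written, very probably by a factor of 1,000. It is a minor point. It deserves correction because it is a stated number in the rule that sets the dose for both groups, not because harm is expected.

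The conclusion rests on two things: the assumed largest hand-muscle response of about 1 to 30 mV, and the reading that the sentence was mis-drafted and not altered by text conversion. The second is likely but not certain.

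Two further readings are tempting and not supported. One is that patients would be overstimulated while operators chase a 50 mV response; nothing in the article suggests that they would. The other is that the comparison of iTBS with rTMS is biased; the same threshold definition and the same 80% apply to both groups. Sample size, power and analysis do not depend on the figure.

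**What to change.** Confirm the unit against the guideline cited in section 2.2.3. Then replace the operational definition with one sentence along these lines: the RMT is the lowest stimulus intensity that produces motor-evoked potentials of 50 microvolts or more in the contralateral first dorsal interosseous muscle in at least 5 of 10 consecutive trials. This corrects the unit and also replaces the references to a bone and to treatments. Check that the operating TMS protocol carries the same criterion.

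The cost is one corrected sentence and one check. Design, sample size and analysis stay as they are.

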#### 2.2.4. Routine medical care

Medical care based on the disease of each patient is permitted.

#### 2.2.5. Discontinuation criteria

Patients with worsening symptoms, such as recurrent stroke, decreased muscle strength, or persistent unexplained infections.

Patients who wish to discontinue participation.

Patients who are unable to complete the treatment sessions.

Patients who are unable to participate in the baseline assessment.

### 2.3. Outcomes

Our primary outcome will be the Montreal Cognitive Assessment Beijing Version (MoCA-BJ) score from baseline to the end of the intervention (D11). Secondary outcomes will be resting EEG indexes, the Auditory Verbal Learning Test (AVLT), the symbol digit modality test (SDMT), the Digital Span Test (DST), and adverse events. Indexes of resting EEG include the absolute power and relative power of neural oscillations. Other outcomes include the Hamilton Depression Scale (HAMD) and Activities of Daily Living (ADL). All clinical assessments will be performed thrice: pre-treatment (baseline), post-last treatment, and at the 1-month follow-up. An experienced physician will conduct all cognitive assessments throughout the study and will be blinded to the participants’ group assignment and trial phases. The resting EEG will be conducted at baseline and at the end of TMS treatment.

#### 2.3.1. MoCA-BJ

The MoCA-BJ is a Chinese version of the Montreal Cognitive Assessment that is highly sensitive and specific for screening cognitive impairment in stroke patients (Nasreddine et al., 2005; Yu et al., 2012).

#### 2.3.2. Resting EEG measurements

A resting EEG is a graphical representation of the spontaneous electrical activity of a population of brain cells. It is obtained by magnifying and recording spontaneous biopotentials of the brain from the scalp using sophisticated electronic equipment (Höller and Nardone, 2021). EEG signals will be recorded using an EEG cap equipped with 64 Ag/AgCl electrodes, arranged according to the Extended International 10–20 electrode placement system (Tamburro et al., 2020). A 5-min EEG recording will be conducted with participants seated comfortably in a sound-insulated, dimly lit room with their eyes closed. All channels will be referenced online to the bilateral mastoid and amplified using an amplifier (Compumedics Neuroscan, Neuroscan 8050). Data will be sampled at 2,048 Hz, with impedances kept below 10 kΩ for all channels throughout data collection.

The acquired EEG signals will be analyzed offline using MATLAB2013b. Given previous evidence that oscillatory dynamics are affected by rTMS (Thut et al., 2011; Veniero et al., 2011; Chota et al., 2021) and are closely related to cognitive improvement (Klimesch et al., 1993; Richard Clark et al., 2004; Iliopoulos et al., 2020), we will analyze the power spectrum and functional connectivity of each oscillation within and between hemispheres, between groups, and pre- and post-treatment. Oscillation ratios, such as θ/α ratio, θ/γ ratio, and (α + β)/(θ + δ) ratio will be further analyzed (Coben et al., 1985; Moretti et al., 2013; Sato et al., 2022).

#### 2.3.3. AVLT

In the neuropsychology literature, AVLT is frequently used to assess memory. The test measures immediate and delayed free recall, retroactive and proactive interference, and recognition through verbal learning (Hawkins et al., 2004).

#### 2.3.4. SDMT

Several cognitive operations require the evaluation of information processing speed, which can be achieved through SDMT (Silva et al., 2018).

#### 2.3.5. DST

The scale can be divided into digit span forward (DSF) and digit span backward (DSB), each of which consists of two sets of 2-digit to 10-digit tables. The total score of the DSF and DSB indicates the participant’s attentional functioning, with a higher score indicating better function (Jahanshahi et al., 2008).

#### 2.3.6. HAMD

Hamilton Depression Scale has been widely used in psychopharmacological and clinical research since the 1960s (Hamilton, 1967).

#### 2.3.7. ADL

The modified Barthel Index (MBI) is used to assess an individual’s ability to perform basic activities of daily living (Mahoney and Barthel, 1965; Shah et al., 1989). In this study, a Chinese version of the MBI that includes ten items (personal hygiene, bathing, feeding, toileting, stair climbing, dressing, bowel control, bladder control, walking or wheelchair transfers, and chair-bed transfers) will be used (Leung et al., 2007). Total independence is indicated by a score of 100.

#### 2.3.8. Adverse events

During the treatment period and within 1 h following each treatment, adverse events, such as headaches, scalp sensations or nociception, temporal and neck muscle pain, and seizures will be recorded.

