## Abstract

**Introduction:**

Intermittent theta burst stimulation (iTBS), a novel mode of transcranial magnetic stimulation (TMS), has curative effects on patients with post-stroke cognitive impairment (PSCI). However, whether iTBS will be more applicable in clinical use than conventional high-frequency repetitive transcranial magnetic stimulation (rTMS) is unknown. Our study aims to compare the difference in effect between iTBS and rTMS in treating PSCI based on a randomized controlled trial, as well as to determine its safety and tolerability, and to further explore the underlying neural mechanism.

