#### 2.1.3. Participant timeline

The study will begin by screening the participants for eligibility. Once the patient’s eligibility has been confirmed, an informed consent form will be signed, and the patient will be randomly assigned to one of the two treatment groups. Clinical assessment and resting EEG measurements will be performed at baseline (D0), after 10 TMS treatments (D11), and at the 6-week follow-up (W6). It is possible that some participants will not be able to attend our hospital for their evaluation at W6. Therefore, we will present two situations. Participants who can return to the hospital will have their EEG data collected at W6, while those who are unable to return to the hospital will be evaluated door-to-door. A record will be made if a patient leaves the trial, is excluded, or withdraws at any point, along with the reasons. The visit schedule and study flowchart are presented in Table 1 and Figure 1.

**TABLE 1 T1:** Trial schedule.

	Trial schedule				
	**Enrollment**	**Allocation**	**Post-allocation**	**Close-out**	**Follow-up**
**Timepoint**	**-D1**	**0**	**D1–D10**	**D11**	**W6**

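### Adverse-event recording stops with treatment, although safety is a stated aim and patients are followed to W6

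*Protocol article*

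**What the plan says.** The Abstract (Introduction) gives safety as part of the study's purpose: "as well as to determine its safety and tolerability". Section 2.3 (Outcomes) ends its list of secondary outcomes with "the Digital Span Test (DST), and adverse events".

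Section 2.3.8 (Adverse events) is the only place that says when these events are collected: "During the treatment period and within 1 h following each treatment, adverse events, such as headaches, scalp sensations or nociception", followed by temporal and neck muscle pain and seizures. The term treatment period is not defined there or elsewhere.

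The surrounding schedule is as follows.

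- Section 2.2 (Interventions): "Each patient will receive TMS stimulation in the afternoon for 10 consecutive days". Table 1 places the interventions at D1–D10.
- Section 2.1.3 (Participant timeline): assessments at baseline, "after 10 TMS treatments (D11), and at the 6-week follow-up (W6"). A patient who cannot return at W6 is visited at home.
- Table 1: cognitive, mood and daily-living scales at baseline, D11 and W6, and resting EEG at baseline and D11. It has no adverse-event row at any time point.
- Section 2.1.3 also has departures from the trial recorded at any time, together with the reasons.
- Section 2.2.5 (Discontinuation criteria) includes "Patients with worsening symptoms, such as recurrent stroke, decreased muscle strength, or persistent unexplained infections".

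**The concern.** The cognitive outcomes are followed for six weeks, but the safety outcome has a collection rule that ends with treatment. A rule that stops early can only lower the number of events counted. A safety statement based on it would describe a shorter period than a reader of a trial with a W6 endpoint would assume.

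The wording also leaves open what is counted during treatment. Two staff members could apply it differently: one might log a headache reported the next morning, while the other might leave it out because it began more than 1 h after the session.

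What is at stake is a stated aim and a secondary outcome. The primary outcome, MoCA-BJ at D11, is not affected.

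**Working it through.** The plan gives no figure for this point, so there is none to reproduce. The check compares the recording window with the follow-up period.

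**Inputs**

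- Treatment days: 10, D1–D10 (section 2.2, Table 1).
- Session length: 10 min in both arms. Section 2.2.1 gives "repeated every 10 s for a total of 10 min and 600 pulses" for rTMS. For iTBS, section 2.2.2 gives 192 s active plus 408 s sham, and 192 + 408 = 600 s = 10 min.
- Time after each session: 1 h (section 2.3.8).
- Last contact: W6, taken as day 42 counted from the start of treatment. This is an assumption, because the article also describes the visit as a 1-month follow-up.

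**Broad reading: treatment period means D1–D10**

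- Covered: 10 of 42 days = 23.8%.
- Not covered: 42 − 10 = 32 days (days 11 to 42 inclusive), and 32/42 = 76.2%.
- Events between sessions are inside the window.

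**Narrow reading: treatment period means the session itself**

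- Covered per day: 10 + 60 = 70 min, and 70/1,440 = 4.9% of each treatment day.
- Covered in total: 10 × 70 = 700 min = 11.7 h.
- Share of 42 days: 11.7/(42 × 24) = 11.7/1,008 = 1.2%.
- An event starting in the evening or overnight after a session is outside the window.

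**From D11 to W6, on both readings**

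- Elapsed time: 42 − 11 = 31 days, none of it in the window.
- If the visit is 1 month (30 days) after D10, it falls on day 40: 40 − 11 = 29 days. On the broad reading, 30/40 = 75% of the period is uncovered.
- If it is 6 weeks after D10, it falls on day 52: 52 − 11 = 41 days. On the broad reading, 42/52 = 81% is uncovered.

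The choice of W6 date therefore moves the gap between 29 and 41 days and does not change the conclusion.

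**Other routes by which an event could be noted after D10**

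- Reasons for withdrawal or exclusion (section 2.1.3): these catch an event only if it ends participation.
- Discontinuation criteria (section 2.2.5): these name events such as recurrent stroke, but do not say that they are recorded as adverse events. A patient who has such an event after D10 and still attends W6 has no entry under section 2.3.8.
- HAMD and ADL at W6: these are scale scores. They may shift after an event but do not identify or count one.

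**The case against.** There is a good case for the plan. Section 2.3.8 uses two terms, a period and each treatment. If the period were only the session, the first term would hardly be needed, so D1–D10 is at least as natural a reading. In that case an evening headache or a seizure on the night after an early session is inside the window. This stands. A reader might infer that all delayed events are lost, or that only 5% of treatment time is watched; the text supports this only on the narrow reading. The argument also runs the other way, since on the broad reading the 1 h clause adds almost nothing. The term is simply ambiguous.

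A reader might also infer that everything after D11 goes unrecorded. That is too strong: section 2.1.3 keeps the reasons for departures at any time, so an event that ends participation leaves a trace. It is not an adverse-event count, and it misses patients who remain in the trial.

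A third tempting inference is that the comparison of the arms is biased. The documents do not support it. The window is the same in both arms and the session length is equalised at 10 min. A difference would require delayed events to be more frequent in one arm, and nothing in the article bears on that.

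The missing adverse-event row in Table 1 is weak evidence by itself, because the table also lacks one for D1–D10, when events are collected. Section 2.3 says that clinical assessments take place three times, but Table 1 lists only scales and EEG, and section 2.3.8 gives adverse events their own narrower rule.

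Finally, a window centred on stimulation is a recognisable choice for tolerability in an exploratory pilot, and an article often leaves serious-event procedures to the full protocol. Both are fair. Here, however, the article states a specific window rather than leaving it open, and that window is shorter than the stated aim needs.

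**Conclusion.** The point holds in limited form. As written, section 2.3.8 stops adverse-event recording by the end of D10 or 1 h after the last session, whichever reading is taken. The interval from D11 to W6, 31 days with W6 as day 42 (29 to 41 days under other readings of the visit date), is not covered except through reasons for withdrawal or exclusion. Whether events between sessions are lost as well depends on an undefined term: coverage of D1–D10 is 4.9% on the narrow reading and essentially complete on the broad one.

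The likely effect is understatement of absolute event counts in both arms. Its size cannot be given, because the article states no event rates. This is a rule badly fixed for a stated aim, not a detail left to another document, and it is cheap to correct.

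**What to change.** In section 2.3.8, define the recording window as first session to W6. Within it:

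- ask the same short checklist before each session, covering the time since the previous one, and again at D11 and at W6, in hospital or at the home visit;
- record any serious event, for example a seizure or recurrent stroke, whenever it occurs in that window, whether or not the patient leaves the trial;
- add an adverse-event row to Table 1 at D1–D10, D11 and W6.

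If the window is to stay as it is, define treatment period and restrict the safety conclusion to acute tolerability during treatment.

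The cost is small. Patients are inpatients treated daily for ten days and are already seen at D11 and W6, so no visit or staff member is added. The downside is slightly more data entry and some background events, unrelated to stimulation, being recorded. The change concerns data collection only; stimulation, schedule and discontinuation criteria are untouched.
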